### Rescue Medications

In case of symptoms of gastritis during the preparatory phase, *Laghusutasekhara rasa* will be administered. During *snehapana*, if there is nausea, vomiting, or episodes of diarrhea, the patient will be observed for stable vitals, and enough hydration will be administered using an oral rehydration solution. If any episodes of dizziness occur during *Vamana* or *Virechana*, enough hydration will be provided with a oral rehydration solution. *Ayoga* (signs and symptoms indicative of inadequate purification) or *Atiyoga* (signs and symptoms indicative of excessive purification) following *Vamana* and *Virechana* will be managed according to the standard textual practices. All such instances will be recorded in the CRF.

### Concomitant Care

The study includes only healthy volunteers; therefore, no concomitant care is needed. If any adverse events occur, they will be managed accordingly. Participants are strictly prohibited from self-administering any over-the-counter antacids, antiemetics, antidiarrheals, or conventional laxatives during the trial, as these would confound the assessment of the purification procedures. Enrolling in external physical therapies, attending commercial spa treatments, or initiating new dietary supplements outside the protocol are also restricted.

### Modifications

In this exploratory study, telomere length was initially included as one of the secondary outcome measures. The challenge with assessing telomere length was identified at the time of recruitment of the first cohort into the study. Lack of local expertise, significant logistics challenges with external testing, and prohibitive costs, all without funding, made measuring telomere length questionable. Hence, telomere length measurement was removed with approval from the institutional ethics committee (IEC), Amrita School of Ayurveda (IEC/ASA.11/27/25) on December 27, 2025. The change was updated in the CTRI (CTRI/2024/02/062176).

### Outcome Measures

#### Primary Outcome

The primary outcome is a decrease in serum MDA levels and increase in serum SOD values. A significant reduction in serum MDA values (baseline and postintervention), indicated by a *P* value <.05, along with a moderate to large Cohen *d* value suggesting a meaningful change will indicate a reduction in oxidative stress levels. A significant increase in SOD activity (baseline and postintervention), indicated by a *P* value <.05, along with a moderate to large Cohen *d* value suggesting a meaningful change reflects an enhanced biological defense mechanism and improved metabolic resilience following the therapy.

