## Methods

### Trial Design

This open-label, exploratory clinical trial consists of a single group and a primary endpoint of decreasing serum MDA values and increasing serum SOD values within 18 days to 20 days after *Vamana* in *Vasantha ritu* and *Virechana* in *Sarad ritu*. The participants will be recruited by the principal investigator consecutively by season: *Vamana* cohort in the *Vasantha ritu* (spring season) and *Virechana* cohort in the *Sarad ritu* (autumn season). Each participant is enrolled into only one seasonal arm based strictly on their chronological window of voluntary registration. There is no active assignment of participants; instead allocation follows a participant-driven, self-selection framework. The total study duration is 3 years. The study is registered in the Clinical Trial Registry-India (CTRI; CTRI/2024/02/062176).

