### Sample Size

The sample size is feasibility-driven. It was chosen based on pragmatic constraints. As this is an exploratory study, the goal is not to achieve definitive statistical power but to establish a foundation for future, larger-scale confirmatory research. Analyzing the census of Kerala, only 30% of the population could be sampled as healthy volunteers excluding NCDs, infectious diseases, other systemic illness like cancer, and age. The sample size was calculated as 53 using the following formula;

$$n=\frac{Z_{1-\alpha /2}^{2}\times P(1-P)}{d^{2}}$$

where Z_1-α/2_=1.96 (assuming a 95% CI), *P*=.5 (expected effeciency/anticipated proportion), and d=0.15 (15% margin of error), assuming a dropout rate of 20%.

Although this sample size is rooted in regional screening feasibility, a retrospective sensitivity power analysis confirmed that a finalized cohort of 53 individuals provides 80% statistical power (*α*=.05) to detect a small-to-medium intra-individual effect size (Cohen *d*=0.395) using a 2-sided paired samples framework. This standard biostatistical validation confirmed that, although the enrollment target is grounded in regional fieldwork constraints, it remains mathematically sensitive enough to capture subtle, homeostatic optimization trends in continuous aging biomarkers (MDA, SOD, and telomerase activity) within a healthy cohort.

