## Discussion

### Theories Underpinning the Study

*Ritu sodhana* or seasonal purification is generally intended to eliminate the seasonal accumulation of humors. This process thereby reduces the susceptibility of seasonal disorders [14]. Acharya Charaka in the context of *Ritu sodhana* has put forth an additional statement that administration of seasonal biopurification will bestow rejuvenation and improve health span [19]. Even though these procedures have been evaluated for their clinical efficacies, its influence on biomarkers for aging has not yet been evaluated. This gap underpins the development of this research protocol, which aims to generate preliminary evidence for this purpose.

*Trikatu Churna,* used for *pachana* and *deepana*, has bioactive constituents including piperine, gingerols, and shogaols and has demonstrated effects on gastric secretion, gut motility, enzymatic activity, splanchnic circulation, and nutrient bioavailability, supporting improved digestive efficiency and systemic absorption [20,21]. This serves as metabolic priming, which is essential to ensure effective digestion and absorption prior to the administration of ghee. *Moorchita ghruta* [22] is widely used in clinical practice. Since the cohort includes healthy volunteers, no other medicated ghee was chosen. *Moorchita taila* [23] was chosen for external application owing to its popularity for the panchakarma procedure. *Trivrut lehya* is used for *Virechanakarma* with limited complications [24].

Based on this framework, we expect that *sodhana* will aid with releasing the waste metabolites, thereby influencing the values of MDA, SOD, and telomerase activity to trigger measurable anti-aging pathway responses across our cohort of 53 healthy volunteers. The hypothesized primary findings include a statistically significant pre-to-postintervention drop in oxidative tissue damage evidenced by a reduction in MDA levels coupled with a significant upregulation of cellular antioxidant defenses, marked by enhanced SOD activity. Furthermore, it is anticipated that this intensive detoxification phase will positively modulate cellular longevity clocks, manifesting as stabilized or elevated telomerase activity, thereby providing an objective, molecular validation of Acharya Charaka’s classical rejuvenation hypothesis.

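### The 80% power holds for one marker on P<.05 alone; the primary outcome names two markers, and power for both at that effect size is about 65–74%

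*Protocol article*

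**What the plan says.** The protocol article names one primary endpoint with two parts. Trial Design describes "a primary endpoint of decreasing serum MDA values and increasing serum SOD values", and Primary Outcome says "The primary outcome is a decrease in serum MDA levels and increase in serum SOD values". In the Discussion, under Theories Underpinning the Study, the expected primary findings are "a reduction in MDA levels coupled with a significant upregulation of cellular antioxidant defenses".

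After its opening sentence, Primary Outcome takes the markers one at a time. Each gets its own criterion (P<.05 together with a Cohen d that is at least moderate) and its own interpretation. Statistical Measures labels 0.5 as a medium effect and uses P<.05 throughout. The article does not say how the two results combine.

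Sample Size gives a single power figure: "a retrospective sensitivity power analysis confirmed that a finalized cohort of 53 individuals provides 80% statistical power" at alpha .05 for Cohen d=0.395, "using a 2-sided paired samples framework". The next sentence applies this sensitivity to MDA, SOD and telomerase activity. The same section calls the sample size feasibility-driven and says definitive power is not the goal.

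**The concern.** A power figure should belong to the outcome it is printed for. This one belongs to a single paired test, whereas the primary outcome joins two markers with the word and. Two tests that must both succeed have less power than either alone. Two tests of which one is enough have more power, but a higher false-positive rate than the alpha quoted. On either reading, 80% power with alpha .05 does not describe the primary outcome.

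The practical stake is a split result, with one marker significant and the other not. The article gives no rule for whether that meets the primary outcome. If the rule is chosen after the data are seen, a one-marker result could be reported as success.

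**Working it through.** **Inputs from the article.** n=53 pairs, d=0.395, two-sided alpha .05, paired test (Sample Size); P<.05 for each marker (Primary Outcome, Statistical Measures); medium effect = 0.5 (Statistical Measures).

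**Assumptions, not in the article.** True d=0.395 on both markers; all 53 pairs complete; correlation r between the two change scores, each signed so that positive means benefit, taken from 0 to 0.8.

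**1. The article's own figure.** The paired t test has 52 degrees of freedom and noncentrality 0.395 × √53 = 2.876. The two-sided 5% critical value is 2.007. The noncentral t gives power of 80.6%; exactly 80% is reached at d=0.392. The stated 80% is therefore right for one marker.

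**2. Both markers at P<.05 in the expected direction.** At r=0 this is 0.8057² = 0.649. For other r it is the bivariate normal probability that both tests succeed, confirmed by simulated paired t tests to within half a percentage point. The chance of a split result is 2 × (0.8057 − joint power).

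| r | Both significant | Exactly one significant |
|---|---|---|
| 0 | 65% | 31% |
| 0.3 | 67% | 26% |
| 0.5 | 69–70% | 22% |
| 0.8 | 74% | 14% |

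Over all possible correlations, joint power runs from about 61% (strongly opposed changes) to 81% (r=1). Joint power of 80% with 53 pairs needs d of about 0.45 on each marker at r=0, or 0.42 at r=0.8.

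**3. Either marker suffices.** Power at r=0 is 1 − (1 − 0.8057)² = 96%. With no true effect, the chance of at least one two-sided P<.05 is 1 − 0.95² = 9.75% at r=0, falling to about 7.8% at r=0.8 by simulation. If only the expected direction counts, the comparison at r=0 is 1 − 0.975² = 4.9% against 2.5% for one test. The inflation is close to twofold either way.

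**4. Adding the Cohen d condition.** P<.05 needs an observed d of only 2.007/√53 = 0.28. If success also needs an observed d of at least 0.5, that condition governs, because t must then reach 0.5 × √53 = 3.64. At true d=0.395 this has probability of about 24% per marker and, by simulation, about 6% (r=0) to 16% (r=0.8) for both.

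**The case against.** The strongest reply is that nothing is miscalculated. Sample Size describes a detectable effect in one paired comparison, the figure reproduces, and joint power is never claimed. This stands: the fault is a correct number attached to an outcome it does not describe. But the section also presents the calculation as validating sensitivity for the whole list of markers, without saying that it is per marker.

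A second reply is that requiring both markers is only a reading. This stands in part. Primary Outcome interprets MDA and SOD separately, and the Discussion passage is expectation, not a decision rule. The joint reading is the better supported one, given a singular primary endpoint and the word and, but it is not explicit. The other reading does not rescue the printed pair, because alpha is then the figure that fails.

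A third reply is that success rules and multiplicity are often left to an analysis plan not shown here. Silence alone would indeed be no finding. The point rests on two printed statements that do not match.

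A fourth reply is that the trial is exploratory and, in its Limitations, calls its sample size pragmatic. This stands and lowers the severity. It does not make a single-marker power figure fit a two-marker outcome.

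A reader might also infer that 65–74% is the power to meet the primary outcome exactly as worded. The article does not support that. The range uses P<.05 alone, whereas Primary Outcome also asks for an at least moderate Cohen d; it rests on an assumed correlation; and the both-required rule is not stated.

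**Conclusion.** The point holds in a limited form. The 80% is correct per marker on P<.05. If both markers are required, it overstates power by about 7 to 16 points against the recomputed 80.6% (80.6 − 73.6 = 7.0; 80.6 − 64.9 = 15.7). This assumes d=0.395 on each marker, complete pairs and r between 0 and 0.8. If either marker suffices, the two-sided error rate is about 8–10%, not 5%. If an observed d of at least 0.5 is a real condition of success, power is far below 80% even for one marker, at about 24%.

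Severity is minor to moderate. The sample size does not depend on this figure and the trial is hypothesis-generating. However, a split result has a 14–31% chance at the article's own effect size, and the article does not say how it would be judged.

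**What to change.** In Sample Size, state that the 80% is per marker on P<.05 alone. Add that power for both markers at d=0.395 is about 65–74% for correlations of 0 to 0.8, and that the correlation is assumed.

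In Primary Outcome, before the pending analysis, settle two things:

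- **How the markers combine.** If both are needed, which is the reading the wording supports, no alpha adjustment is required and one significant marker does not meet the primary outcome. If each is a separate primary outcome, either split alpha or state that the familywise error is not controlled.
- **The role of Cohen d.** Say whether it is part of success or only descriptive. If it is part of success, give the threshold and the matching power, since 65–74% would no longer apply.

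The cost is a few sentences and no additional participants. The stated power becomes less favourable, and under the joint rule a one-marker result would have to be reported as not meeting the primary outcome.

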### Statistical Measures

The change in values of the outcome measures including MDA, SOD, telomerase activity, and telomere length will be recorded. The data will be tested for normality using the Shapiro-Wilk test. They will be tested for significance using paired *t* tests (if the data are normally distributed) or the Wilcoxon Signed Rank test (if the data are not normally distributed). A *P* value <.05 will be considered significant. All statistical analysis will be conducted using SPSS version 31 (IBM Corp). Moreover, a secondary exploratory subgroup analysis will be conducted within and between the 2 cohorts (*Vamana* and *Virechana* groups) based on the distribution of the data. If the data are normally distributed, within-group analysis will be conducted using paired *t* tests and between-group analysis will be conducted with *t* tests, whereas Wilcoxon Sign Ranked tests and Mann-Whitney *U* tests will be used, respectively, for data that are not normally distributed.

Cohen *d* effect sizes will also be calculated to address the exploratory nature of the study and evaluate the clinical and biological relevance of changes in biomarkers (ie, MDA, SOD, and telomerase activity). Results will be interpreted based on the magnitude and directionality of these effect sizes (small: 0.2; medium: 0.5; large: 0.8) to provide a standardized measure of treatment impact beyond simple *P* value testing.

Given the exploratory, hypothesis-generating design of this pilot study, secondary multivariable analyses will be introduced to evaluate the influence of potential baseline confounders. For normally distributed continuous data, an analysis of covariance (ANCOVA) will compare postintervention outcomes between the 2 seasonal subcohorts (*Vamana* vs *Virechana*) using individual pre-intervention scores as the baseline covariate to mathematically adjust for initial biological variation. Additionally, to evaluate the entire cohort of 53 participants as a unified group, multiple linear regression models will be constructed using the postintervention scores as the dependent variable, entering baseline biomarker values, age, sex, and baseline BMI as independent predictors to systematically control for demographic and physical confounding variables.

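### The 80% power quoted at d=0.395 applies to the P value alone; the plan also asks for a moderate to large Cohen d, and with a floor of 0.5 the full criterion is met only about 24% of the time at that effect

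*Protocol article*

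**What the plan says.** **Outcome Measures, Primary Outcome.** Each marker is given two conditions. For MDA, a P value below .05 "along with a moderate to large Cohen *d* value suggesting a meaningful change will indicate a reduction in oxidative stress levels". SOD has a parallel sentence with its own conclusion. Secondary Outcomes applies the same pair of conditions to telomerase activity.

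**Statistical Measures.** The only numeric benchmarks for d in the article are "small: 0.2; medium: 0.5; large: 0.8". They are offered as a guide to the magnitude and direction of effects. They are not expressly called lower bounds, and the section does not say which standard deviation goes into d.

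**Sample Size.** A retrospective sensitivity analysis is reported: "a finalized cohort of 53 individuals" "provides 80% statistical power" at α=.05, "using a 2-sided paired samples framework", for a Cohen d of 0.395 that the section labels small-to-medium. From this it concludes that "it remains mathematically sensitive enough to capture subtle, homeostatic optimization trends in continuous aging biomarkers" such as MDA, SOD and telomerase activity. The same section describes the sample as feasibility-driven and says that definitive power is not the goal.

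**The concern.** The effect used to show that the trial is sensitive enough is smaller than the medium benchmark, while the outcome sections ask for at least a moderate d before a change is read as meaningful. The power statement therefore covers one of the two conditions and says nothing about the other, which turns out to be the stricter.

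Two things are at stake. A reader who takes the 80% at face value will expect an effect of 0.395 usually to be reported as a meaningful change, when under the natural reading it usually would not be. And because moderate has no stated floor and d no stated denominator, whether a given result meets the criterion could be settled after the data are seen.

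**Working it through.** **Inputs.** n=53 pairs, two-sided α=.05, paired framework, true d=0.395 (Sample Size); P<.05 together with a moderate to large d (Primary and Secondary Outcomes); medium=0.5 (Statistical Measures). Two readings are assumed: moderate means an observed d of at least 0.5, and d is mean change divided by SD of change. The second fits the intra-individual, paired wording of the power statement.

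**1. Reproduce the stated power.** The paired t statistic follows a noncentral t distribution with 52 degrees of freedom and noncentrality d×√n = 0.395×√53 = 2.876. The critical value is 2.007. P(T>2.007) = 80.6%. The stated 80% is confirmed; exactly 80% corresponds to d=0.392.

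**2. Which condition binds?** With this definition, observed d = T/√n. P<.05 needs an observed d of only 2.007/√53 = 0.276. An observed d of 0.5 means T = 0.5×√53 = 3.640, for which two-sided P = 0.0006. Any result that meets the 0.5 floor is therefore already significant, and the d condition alone decides.

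**3. Chance of meeting the full criterion, one marker, floor 0.5.** This is P(T>3.640) with noncentrality d×√53:

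| True d | P<.05 alone | P<.05 and observed d ≥ 0.5 |
|---|---|---|
| 0.395 | 80.6% | 24.1% |
| 0.5 | 94.7% | 50.7% |
| 0.6 | 99.0% | 75.9% |
| 0.62 | 99.3% | 79.9% |

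**4. Vary the floor, true d=0.395.**

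| Floor for observed d | Chance of meeting both conditions |
|---|---|
| 0.30 | 75% |
| 0.35 | 63% |
| 0.40 | 49% |
| 0.45 | 36% |
| 0.50 | 24% |

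Any floor above 0.276 lowers the figure below that of the paired test alone, and every floor tabulated is below 80%.

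**5. Vary the definition of d, floor 0.5.** If d used the SD of the scores, the result would depend on the pre-post correlation, which the article does not give. Simulation with an assumed correlation of 0.3, 0.5 or 0.7, keeping the standardised change at 0.395, gives 43%, 24% or 5%.

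**6. Fewer pairs.** The Sample Size section also assumes 20% dropout. Applied to 53 this leaves 53×0.8 = 42.4, or 42 pairs: 70.5% on the P value alone and 26.7% on the full criterion. The conclusion is unchanged.

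**The case against.** **The 0.5 floor is inferred.** This stands in part. The article never writes a cut of 0.5; it lists benchmarks and itself calls 0.395 small-to-medium, as if d were a continuum. The 24% is therefore conditional. But no other value for medium is given, and floors from 0.30 to 0.45 still leave the criterion short of 80%.

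**The power sentence is correct.** It is. It describes a paired test and never claims to cover a joint criterion. A reader might infer that the 80% is a miscalculation; the recalculation shows otherwise. What is wrong is the use made of it: it supports a claim of sensitivity to subtle changes that the outcome sections would often not count as meaningful.

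**Requiring significance plus relevance is legitimate.** Agreed. A pass rate near 50% when the true effect equals the threshold is a property of any cut on a point estimate and not peculiar to this trial. Nor would deleting the d condition be a clear improvement: at a true d of 0.2, P<.05 alone is met about 30% of the time, against about 2% with a 0.5 floor. In an uncontrolled pre-post study that protection has value.

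**The trial is exploratory.** This also stands and lowers the weight. The outcome sections say how a result will be interpreted; they do not set a formal success rule, and Limitations calls the sample size pragmatic. The Dissemination Policy commits to submission for publication whatever the findings.

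**Both markers.** A reader might infer that MDA and SOD must both pass, which would make the chance smaller still. The article does not say so: it interprets each in its own sentence with its own conclusion. The figures here are therefore per marker.

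**Conclusion.** The concern holds as an inconsistency between the stated sensitivity and the stated interpretation criterion. The 80% at d=0.395 is right for the paired test (80.6%) but does not describe the two-part criterion. With a floor of 0.5 and d based on the SD of change, that criterion is met for one marker about one time in four at the advertised effect, about half the time at 0.5, and 80% of the time only at a true d of about 0.62. The exact size rests on those two readings; that it falls short of 80% holds for every floor and every assumed correlation examined.

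The documents do not support the stronger reading that the trial is underpowered for a formal success rule, because they set no such rule and disclaim definitive power. This should be fixed, but it does not threaten the validity of the trial.

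**What to change.** 1. **Sample Size:** state that 80% power at d=0.395 refers to the P<.05 condition only. Add the sensitivity under the full criterion; with a floor of 0.5 and d based on the SD of change, this is about 80% at a true d of about 0.62. Drop the claim about subtle trends, or limit it to detection by the paired test.
2. **Primary and Secondary Outcomes:** give the numeric floor meant by moderate, say which standard deviation d uses, and report d with its 95% CI. The mean change with its SD and 95% CI is already promised under Core Outcome Set and Summary Measures.

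Removing the d condition, or requiring both MDA and SOD to pass, is optional and a matter of judgement; neither is needed to resolve the inconsistency.

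The cost is a few sentences and a less favourable stated sensitivity. No change to sample size or data collection is needed. The Results section says that data analysis is pending, so the wording can be settled before results are seen.
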